## Abstract

**Background:** Despite intravenous thrombolysis and endovascular therapy for acute ischemic stroke (AIS), many survivors still have varying degrees of disability. Glyceryl trinitrate (GTN), a nitric oxide (NO) donor, has been previously reported to induce neuroprotection after AIS. The use of GTN to reduce brain damage after stroke remains yet to be elucidated. This study was designed to explore the safety, feasibility, and preliminary efficacy of intravenous administration of GTN after AIS.

**Methods:** A prospective randomized controlled trial is proposed with AIS patients. Participants will be randomly allocated to GTN group and control group with a 1:1 ratio (*n* = 40). Both groups will be treated with standard therapies according to the current stroke guidelines. Participants allocated to the GTN group will receive intravenous administration of GTN (5 mg GTN in 50 ml saline at a rate of 0.4 mg/h that is continued for 12.5 h/day for 2 days) within 24 h of symptom onset. Participants allocated to the control group will receive intravenous administration at equal capacity of 0.9% normal saline (NS) (total 50 ml/day at 4 ml/h that is continued for 12.5 h/day for 2 days). The primary outcome is safety [systolic blood pressure (SBP) <110 mmHg, headache], while the secondary outcomes include changes in functional outcome and infarction volume.

**Discussion:** Rapid Intravenous Glyceryl Trinitrate in Ischemic Damage (RIGID) is a prospective randomized controlled trial that aims to ascertain the safety, feasibility, and preliminary efficacy of intravenous GTN as a neuroprotection strategy after AIS. These results will provide parameters for future studies as well as provide insights into treatment effects. Any possible neuroprotective qualities of GTN in AIS will also be elucidated.

**Trial Registration:**www.chictr.org.cn, identifier: ChiCTR2100046271.

## Introduction

Due to its high rate of mortality and morbidity, ischemic stroke is a devastating public health concern that also results in high socioeconomic burden (1–4). The effective treatments for acute ischemic stroke (AIS) are intravenous thrombolysis and mechanical thrombectomy. Due to the narrow time window for intravenous alteplase [tissue plasminogen activator (tPA)] of 4.5 h, the majority of patients are not eligible for this treatment. In addition, two-thirds of stroke patients still suffer from varying degrees of disability (5, 6) even after intravenous thrombolysis. Endovascular therapy (within 6 h of stroke and up to 24 h) has shown great benefit in improving functional outcomes in AIS patients with large vessel occluded (LVO) in the anterior circulation. However, only 46% of the patients achieve functional independence at 90 days with a 15.3% mortality rate (7). In the EXTEND trial (8), patients benefited from tPA between 4.5 and 9.0 h after the onset of stroke. This study suggested that the “tissue window” has advantages over the traditional “time window” in screening patients. Thus, exploring fast and effective neuroprotection strategies to save ischemic penumbra and to lengthen the “tissue window” may be the key in the treatment of AIS.

Ischemic stroke-induced brain damage results from the interaction of complex pathophysiological processes such as excitotoxicity, oxidative stress, inflammation, and apoptosis (9). NO has a central role in hypoxic signaling, and its physiologic and therapeutic levels exert potent cytoprotection after ischemia and reperfusion in various tissues including the brain (10). NO derived from endothelial nitric oxide synthase (eNOS) plays a critical role in the regulation of cerebral microvascular tone, the protection of the blood–brain barrier, the reduction of oxidative stress, and the alleviation of procoagulant stimulation (11–13). Various animal studies have reliably demonstrated a loss of cytoprotection when subjects were treated with NO scavengers or when NOS was inhibited or knocked out (14–16). NO donors are a heterogeneous group of drugs whose common feature is the ability to release NO or an NO-related species *in vitro* or *in vivo* independently of endogenous sources (17). NO donors have been implicated in improving cancer therapy, hypertension, and peripheral artery disease (17). Several preclinical studies suggest that NO donors could safely reduce infarct size, increase cerebral blood flow, and improve functional outcome in AIS in both transient and permanent stroke models (18). The neuroprotective effect of NO donors has been previously demonstrated to work at many different levels by several mechanisms including that of altering the cellular oxidative status, inhibiting monocyte activity, and diminishing primary hemostasis (19).

GTN, a Food and Drug Administration-approved vasodilator, is an example of a drug that functions as a NO donor. Transdermal GTN had been found to lower blood pressure (BP), have no deleterious effects on platelet function, and exert no changes in the middle cerebral artery blood flow velocity or regional cerebral blood flow in AIS patients (20–23). A recent larger sample size randomized controlled trial (RCT) to determine the efficacy of transdermal GTN for the management of high BP in AIS (ENOS) also revealed the potential to reduce BP without finding a functional improvement following AIS if administered within 48 h (24). However, this study indicated that administration of GTN within 6 h improved functional outcomes. The RIGHT-2 trial (25) focused on the safety and efficacy of transdermal GTN given within 4 h of onset of AIS assessed in the prehospital environment in the UK. This trial did not show that prehospital treatment with transdermal GTN improved functional outcomes in patients with presumed stroke. Importantly, the neuroprotective effect of NO donors after ischemia–reperfusion injury (IRI) has yet to be reported consistently with many factors contributing to this including dose, location, source, and environment (26). Further protocols have been proposed to evaluate the use of transdermal GTN in acute stroke treatment (26). In light of these parameters and owing to the short half-life of GTN, GTN administration as a patch on the arm or chest may not reach an effective concentration in the cerebrovascular system. As such, a continuous intravenous administration of GTN may be a rapid and effective way to maximize any benefit of this drug (26). Furthermore, 24-h continuous GTN administration can cause tolerance resulting in subtherapeutic levels. This knowledge hints that a better outcome may be possible if an “intermittent” therapy is used (27–29). At present, no study has been reported on the safety and efficacy of intravenous GTN as an adjuvant neuroprotective strategy for AIS. We have consequently designed this single-center, prospective RCT to evaluate the safety, feasibility, and preliminary efficacy of intravenous administration of GTN after AIS.

## Methods

### Study Design

This study is a phase 1, single-center, prospective RCT. Participants will be patients with AIS within 24 h onset. Patients meeting the inclusion criteria but not the exclusion criteria will be randomly allocated to the GTN group or the control group. Both groups will be treated with the standard management according to the guidelines (30). GTN will be administered by continuous intravenous pump (5 mg GTN in 50 ml saline with a speed of GTN 0.4 mg/h continued for 12.5 h/day for 2 days) within 24 h of symptom onset in the GTN group. The control group will receive intravenous administration of equal capacity of 0.9% normal saline (NS) (total 50 ml/day at 4 ml/h continued for 12.5 h/day for 2 days). The clinical characteristics, medical history (diabetes, hypertension, hyperlipidemia, coronary heart disease, stroke, atrial fibrillation), smoking history, alcohol drinking history, and National Institutes of Health Stroke Scale (NIHSS) score at admission will be collected. Magnetic resonance imaging (MRI) will be performed at baseline and on day 7 ± 1. NIHSS and modified Rankin Scale (mRS) will be assessed at baseline and on days 1, 7, 14, 30, and 90.

All participants or proxies will be informed of potential risks and possible benefits and consent to this study. This consent will be provided to a legal representative if the patients do not have the capacity to consent. This study was approved by the ethics committee of Luhe Hospital, Capital Medical University, Beijing, China, and has been registered at www.chictr.org.cn with ChiCTR2100046271. An independent physician will monitor the health and safety of the participants.

### Patient Population: Inclusion and Exclusion Criteria

Participants will be recruited from the stroke center [the Stroke Intervention & Translational Center (SITC)] in Beijing Luhe Hospital (Figure 1). The inclusion criteria are (1) ≥18 and ≤ 80 years old, (2) clinical diagnosis of AIS, (3) systolic blood pressure (SBP) ≥120 mmHg, (4) NIHSS score ≥3 and ≤ 16, (5) patients with time from onset to treatment ≤ 24 h who did not receive endovascular treatment (EVT), (6) prestroke mRS ≤ 2, and (7) informed consent provided by participant or legally authorized representative.

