### Randomization and Blindness

During the recruitment period, participants will be allocated 1:1 to two groups (*n* = 40) by computer-generated randomization procedures using opaque envelopes. A research assistant not involved in the study will prepare the envelopes before the study. After recording baseline measures, participants will be randomly allocated to either the intervention or the control group by the treating physicians, who will open the sealed opaque envelopes. In order to minimize selection bias, patients and assessors involved in the trial will be masked to the treatment allocation. All outcome measurements will be assessed by two observers who will be blinded to the treatment plan. Any disagreement will be resolved by reaching a consensus between the two. If no consensus can be reached, a third observer blinded to the treatment assignment and not involved in the clinical treatment plan will have the final decision. Finally, an independent investigator blinded to the treatment assignment will collect the data of outcomes and information of the group and analyze them.

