#### Secondary Outcomes (Efficacy Assessment)

The primary efficacy outcome is the mRS at 90 days (mRS scores of 0–2 indicate functional independence). Secondary efficacy outcomes include the rate of the 0–2 mRS at 90 days, the incidence of death at 90 days, blood nitrate index detection at 1 day [cyclic guanosine monophosphate (cGMP, second messenger to NO), L-arginine (substrate for NO), and L-citrulline (co-product with NO)], infarct volume, as well as NIHSS scores at days 1, 7, 14, 30, and 90. The mRS and NIHSS scores will be obtained by a blinded personnel to the research. Face-to-face encounters in the consultation room will be used in the study to calculate mRS and NIHSS. Brain infarct volume will be determined by MRI diffusion-weighted imaging technique. The lesion profile plotted at each individual level by an image tool [region of interest (ROI)] on the workstation will be used to calculate the area. The levels will be multiplied by the thickness of each level and summed to calculate the infarct volume. The calculations will be performed by personnel blinded to clinical data and randomization at baseline and at day 7 ± 1.

Patients diagnosed as AIS without corresponding lesions on MRI are rare (<2%) in our stroke center. Patients who are misdiagnosed with stroke through negative MRI will be reported, and subgroup analysis will be performed.

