NO plays a pivotal role in preventing inflammation and attenuating oxidative stress after IRI, and, therefore, NO supplementation using NO donor drugs is a reasonable approach to minimizing the cerebral damage after ischemia. GTN is one of the most widely used exogenous NO donors in the clinic. Three studies (20–22) on transdermal GTN in acute stroke showed that GTN lowered peripheral and central BP, 24-h BP, pulse pressure, and augmentation index. However, RCTs ENOS (53) and RIGHT-2 (25) on transdermal GTN patch (5 mg) showed that there was no significant change in functional or secondary outcomes measured at day 90. In a prespecified subgroup analysis of participants within 6 h of stroke presentation in the ENOS trial, those who received GTN had a favorable improvement in functional outcomes, less death and disability, and improved cognition (25). Transdermal GTN is a simple method to the delivery of GTN; however, not all of the drug released from the patch reaches the systemic circulation (54). Compared with intravenous administration, about 75% of nitroglycerin is systemically bioavailable after patch administration (55). The reason for lost drug is related to retention at the application site, tissue binding, and breakdown (33). The development of an intravenous form of nitroglycerin has further enhanced the role of nitrates in the therapy of cardiovascular disorders. Intravenous form of nitroglycerin permits prompt initiation of therapy and rapid attainment of high systemic levels (56). Although there is concern that lowering BP may worsen outcomes in the context of carotid stenosis, an analysis of the ENOS trial demonstrated that transdermal GTN appeared safe in both ipsilateral and bilateral stenoses (25). Considering that both GTN and NO (57) have a very short half-life in the body, an intravenous form of nitroglycerin with rapid dose titration is both feasible and safe. This may be the best method in a clinical trial for stroke patients to receive targeted cerebral NO donors. Prior clinical trials on the continuous application of nitroglycerin patches showed that 24-h continued use of GTN results in developing tolerance in the majority of patients with stable angina and suggested that “intermittent” therapy may provide a more rational approach to therapy. With removal of the patch for 10–12 h in each 24-h period, this will provide a patch-free period, which may allow the reestablishment of sensitivity (27–29). The daily dose at 5 mg/day [0.4 mg/h (54)] was recommended in the two important RCTs ENOS and RIGHT-2 on transdermal GTN patch (25, 58). In order to rescue the ischemic penumbra that infarct completed within 48 h after stroke onset (59), GTN at a speed of GTN 0.4 mg/h for 12.5 h/day, which makes 5 mg/day in total, was used in the present study, for 2 days. We will determine whether intravenous GTN is safe and has the potential to improve functional outcomes in patients with AIS.

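### The 48-hour penumbra rationale does not cover the second infusion of late entrants, and the stated efficacy tests take no account of time since onset

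*Protocol article*

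**What the plan says.** **Entry.** The inclusion criteria admit "patients with time from onset to treatment ≤ 24 h who did not receive endovascular treatment (EVT".

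**Schedule.** Study Design and Interventions give 12.5 h of infusion per day for 2 days, starting within 24 h of onset. The interval between the two infusions is not stated.

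**Rationale.** The Discussion gives the reason for two days: "In order to rescue the ischemic penumbra that infarct completed within 48 h after stroke onset (59".

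**Evidence on timing.** The Introduction describes a large transdermal GTN trial that was neutral overall within 48 h, then adds that "this study indicated that administration of GTN within 6 h improved functional outcomes". The Discussion identifies this as a subgroup result. The Introduction also reports a prehospital trial of treatment within 4 h: "This trial did not show that prehospital treatment with transdermal GTN improved functional outcomes in patients with presumed stroke".

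**Imaging.** MRI is done at baseline and on day 7 ± 1. On infarct volume: "The calculations will be performed by personnel blinded to clinical data and randomization at baseline and at day 7 ± 1". The abstract presents this outcome as a change.

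**Allocation and analysis.** "participants will be allocated 1:1 to two groups (*n* = 40) by computer-generated randomization procedures using opaque envelopes". Statistical Analyses names a t-test or Mann–Whitney test for NIHSS and infarct volume, and χ², Fisher or continuity-corrected tests for proportions. The one subgroup named is MRI-negative patients. Progression to phase 2 depends on adverse reactions and on finding no difference in 90-day prognosis.

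**The concern.** Two things do not fit together.

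First, the two-day regimen is argued from a clock that starts at stroke onset and ends at 48 h. The schedule starts at treatment, which may be as late as 24 h. For later entrants the second infusion may therefore fall partly or wholly outside the period that justifies it.

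Second, if the lesion is evolving until 48 h, a baseline scan at 3 h and one at 23 h do not measure the same thing. Apparent growth to day 7 depends on when the first scan was taken. The same elapsed time may bear on NIHSS and mRS. The analysis as stated compares the arms without using this time, so any chance difference between them in onset time passes straight into the comparison.

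At stake are the exploratory efficacy estimates meant to inform phase 2, and the 90-day part of the progression rule.

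**Working it through.** **1. The plan's own figure.** The sample size uses a difference of 10 mmHg and an SD of 10 mmHg, with the error rates read as two-sided α = 0.05 and power 0.80. Then n per group = 2 × (1.96 + 0.84)² × (10/10)² = 15.7, rounded up to 16. Allowing 20% loss gives 16/0.8 = 20 per group, or 40 in total. This reproduces the stated 16 and 40. Onset time does not enter, so neither figure changes.

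**2. Timing of the second infusion.** Let T be hours from onset to the first infusion and s the interval between the two starts. The second infusion runs from T + s to T + s + 12.5. It passes 48 h when T > 35.5 − s. Hours after 48 h = T + s − 35.5, bounded between 0 and 12.5.

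With s = 24 h (assumed):

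| T (h) | Second infusion (h from onset) | Hours after 48 h | Share of second infusion |
|---|---|---|---|
| 6 | 30 to 42.5 | 0 | 0% |
| 11.5 | 35.5 to 48 | 0 | 0% |
| 18 | 42 to 54.5 | 6.5 | 52% |
| 24 | 48 to 60.5 | 12.5 | 100% |

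At T = 24 h, 12.5 of the 25 infusion hours (50%) fall after 48 h.

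**3. Sensitivity to the spacing.** The Discussion mentions a patch-free gap of 10–12 h. Applied to these infusions, that gives s = 12.5 + 10 = 22.5 h to 12.5 + 12 = 24.5 h. The threshold 35.5 − s then lies between 13 h and 11 h. At T = 24 h the hours after 48 h are 11 (88% of the second infusion) with s = 22.5 and 12.5 (100%) with s = 24.5. The conclusion does not hinge on exactly 24 h.

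**4. How many patients.** The article gives no distribution of entry times. If they were uniform over 0–24 h (an assumption), the share with some of the second infusion after 48 h would be (24 − 11.5)/24 = 52% with s = 24, ranging from 11/24 = 46% (s = 22.5) to 13/24 = 54% (s = 24.5).

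**5. Chance imbalance in onset time.** Suppose K of 40 patients are early and 20 are allocated to each arm. The number of early patients in one arm is hypergeometric. The probability that the arms differ by at least 4 early patients (20 percentage points) is:

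| K early of 40 (assumed) | Probability |
|---|---|
| 4 | 11% |
| 6 (5:1 or worse) | 18% |
| 10 (7:3 or worse) | 27% |
| 14 (9:5 or worse) | 32% |
| 20 | 34% |

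K is unknown, so this range is the result. It shows that a visible imbalance is ordinary at this size. It does not show how far the imbalance would move the outcomes, because the article gives no figure linking onset time to infarct growth or mRS.

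**The case against.** **A condensed article may leave stratification and covariates to the full protocol or analysis plan.** This stands as far as absence goes. Missing stratification is not the point made here, and adjustment may be specified elsewhere. What the article does state is a set of unadjusted tests for outcomes whose baseline is taken at varying times, and that choice can be improved.

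**A reader might infer that the 24-h window contradicts the article's own evidence for treatment within 6 h.** The text does not support this. The 6-h result is one subgroup finding, and the same paragraph reports a trial within 4 h without functional benefit. A broad window is a legitimate choice in a first intravenous pilot, and entry by 24 h does not conflict with infarct completion at 48 h. Nor can one say that a benefit is diluted to its early-treated share, since nothing establishes that benefit is confined to those patients.

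**The main purpose is safety.** This stands. The primary outcome is mean SBP below 110 mmHg over 24 h, and nothing in the article ties it to onset time.

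**Randomisation already protects the comparison.** It prevents systematic bias, and chance imbalance is expected for any prognostic factor at 20 per arm. Onset time merits attention here because the article's own rationale says the lesion changes over the interval in which baseline is measured, and because this time must already be ascertained for eligibility.

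**Conclusion.** The point holds in a limited form. On the article's own figures, the 48-h rationale does not cover all of the second infusion for patients who start after roughly 11 to 13 h, and covers almost none or none of it for a start at 24 h. This rests on an assumed interval of 22.5 to 24.5 h between starts.

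Separately, the stated tests leave the exploratory infarct-volume, NIHSS and mRS comparisons exposed to chance imbalance in onset time. A gap of at least 20 percentage points in the early-treated share occurs in about 11% to 34% of allocations, for an assumed 4 to 20 early patients. The effect is added noise, which could create or hide a difference in 90-day prognosis and so reach the progression rule. Its size on the outcome scale cannot be derived from the article.

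The SBP primary outcome, the 16 per group and the total of 40 stand. The entry window is not an error.

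**What to change.** 1. **Adjust the efficacy comparisons.** For infarct volume, adjust for onset-to-baseline-scan time together with baseline volume. For NIHSS and mRS, adjust for onset-to-randomisation time. Report the unadjusted result alongside. Onset-to-randomisation time is preferable to onset-to-treatment time because it is known before the envelope is opened. The article has baseline measures recorded before allocation; the plan should confirm that this includes the MRI, so that scan time is also a pre-randomisation covariate.

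   *Cost:* analysis wording, and recording of scan and randomisation times. Two covariates reduce the residual degrees of freedom in a two-group linear comparison of 40 patients from 38 to 36.

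2. **Reconcile the text.** Bring the 48-h rationale in the Discussion into line with the entry window in the inclusion criteria and the schedule in Study Design, and limit the penumbra-rescue claim to what the schedule covers. No change to dose, schedule or window is proposed.

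   *Cost:* wording only.

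Stratified allocation and estimates by time stratum are optional. Treating physicians open the envelopes, so small blocks within strata could make allocations easier to predict. With about 5 early patients per arm, estimates would be close to uninformative: for assumed mRS 0–2 rates of 50% and 70%, power is about 9%, against about 25% with 20 per arm.

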**Figure 1 F1:**
[figure not shown]
Trial randomization flowchart. AIS, acute ischemic stroke; NIHSS, national institutes of health stroke scale; SBP, systolic blood pressure; mRS, modified rankin scale; GTN, glycerly trinitrate; HGB, hemoglobin.

Exclusion criteria are as follows: (1) severe anemia, hemoglobin (HGB) 60 g/L, (2) allergy to GTN, (3) glaucoma, (4) participant in another ongoing clinical trial, and (5) life expectancy of shorter than 1 year due to comorbidities.

